#### Linear Regression on Systolic Blood Pressure Without Exclusion of Participants Treated With Antihypertensive Drugs

As previously mentioned, we believe that any potential effect of occupational lifting on SBP may be concealed, reversed, or otherwise distorted by effects from antihypertensive drugs and other types of heart medications. It is, however, relevant to investigate the effect of the decision to exclude participants who were treated for antihypertensive drugs from sensitivity analysis 1 and, therefore, we will repeat the steps of that analysis, without the exclusion of medically treated participants.

### Substudy on Cardiac Damage

Data from the fourth and fifth examinations of the Copenhagen City Heart Study will be included for the cross-sectional and long-term associations between heavy occupational lifting and cardiac damage in a nested design. Early subclinical structural changes of the heart will be recognized by advanced echocardiographic analyses. We will compare participants exposed to heavy occupational lifting (cases) with matched participants who are not exposed to heavy occupational lifting (controls) both in the cross-sectional and longitudinal study. Controls will be matched on age and sex. Echocardiographic assessment will focus on early subclinical changes in cardiac structure primarily assessed by cardiac mass, indices of diastolic function, and global strain assessments. Analyses will be adjusted for confounders, including hypertension, diabetes, and BMI. With 200 exposed and 200 unexposed participants included in the echocardiographic analyses, we will have 80% power to detect a between-group difference of 1 in global longitudinal strain (equal to 5% difference based on an expected mean of 20) with a significance level (alpha) of 1.25%. The choice of alpha is adjusted to allow for comparison over several parameters of subclinical structural changes.

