## Introduction

### Background

Hypertension is a major risk factor for cardiovascular diseases [1,2] and is responsible for 14% of all annual deaths globally [1]. The prevalence of hypertension varies across occupational groups, possibly affected by differences in the working environment. One work-related factor that might impose a risk for hypertension is lifting [3,4]. Heavy lifting causes acute large increases in blood pressure (BP) [5]. These increases in BP during heavy lifting are explained by the constriction of the vessels due to contraction of muscle fibers surrounding the vessels as well as the pressor reflex, both leading to an increased peripheral resistance and thereby also an increased BP [5]. Thus, because some workers perform occupational lifting for several hours per day, many days per week, higher BP or hypertension is likely to occur [6]. Yet, scientific knowledge of the relation between heavy occupational lifting and hypertension is limited. Previous studies investigating this relation have found occupational lifting to increase risks for myocardial infarction [3] and ischemic heart disease [4] in population studies including both sexes and workers from white- and blue-collar occupations. However, one study, only including males from blue-collar occupations did not find increased risk for ischemic heart disease from occupational lifting [7]. As the study by Petersen and colleagues [4] found the risks from lifting to be most pronounced among workers with low occupational physical activity (OPA) but high exposure to lifting, it seems that investigations of associations between occupational lifting and risk for hypertension benefit from populations including both sexes and a variety of occupations.

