Conversely, heavy lifting might also impose beneficial effects on BP, since resistance training involving heavy lifting has been shown to reduce resting BP [8,9]. Additionally, it is also unknown whether effects of exposure to heavy occupational lifting differ between participants with and without preexisting hypertension. A Danish survey from 2016 [10] concludes that 22% of the Danish workforce are exposed to occupational lifting during ≥25% of their working hours. Likewise, 32% of European workers report to carry or move heavy loads regularly during working hours (6th survey in Eurofound). Thus, an investigation of the association between occupational lifting and risk of hypertension in population studies including both sexes and both blue- and white-collar occupations, might uncover a potential for prevention of cardiovascular diseases for a quite large proportion of the working population.

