### Objective

The aim of this study is to explore associations between heavy occupational lifting and hypertension in the Copenhagen City Heart Study. Associations will be investigated both cross-sectionally and prospectively, among randomly selected citizens from two districts of Copenhagen, Denmark.

For the cross-sectional analysis, the primary null-hypothesis is that there is no association between heavy occupational lifting and hypertension. For the prospective analysis, the primary null-hypothesis is that there is no association between heavy occupational lifting at baseline and increased resting systolic BP (SBP) 10 years later.

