### Implications of the Proposed Analysis

Since one-third of the workforce in Europe reports to carry or move heavy loads regularly during working hours (6th survey in Eurofound) and hypertension is a major risk factor for cardiovascular disease and mortality [1;2], a positive association between occupational lifting and risk for hypertension could reveal a potential for improved prevention for hypertension by reducing exposure to occupational lifting in the population. This could, for example, be achieved by using technical lifting devices and automatization of manual work tasks currently requiring heavy lifting. This is particularly the case because a positive association could be considered as a reflection of a physiological mechanism and therefore must be assumed to apply for the majority of humans exposed to occupational lifting. Conversely, a negative association would not be assumed as a reflection of a physiological mechanism before the negative association had been verified in populations not subject to restrictive regulations of occupational lifting, as employees in Denmark are. Moreover, a null finding would also propose a need for additional investigations of this association in populations with wider ranges of exposure to occupational lifting. Since these proposed analyses will be applied to a randomly selected adult population and is planned to be verified in another randomly selected adult Danish population, these results may be generalized to the Danish adult population engaged in work including occupational lifting.

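### The cardiac substudy adjusts for hypertension as a confounder, although the article's own hypothesis makes hypertension a consequence of lifting

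*Protocol article*

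**What the plan says.** The Protocol article, Substudy on Cardiac Damage, sets out to study "cross-sectional and long-term associations between heavy occupational lifting and cardiac damage in a nested design". Exposed participants are matched to unexposed ones on age and sex, and the outcomes are cardiac mass, diastolic function and global strain. The only adjustment described is "Analyses will be adjusted for confounders, including hypertension, diabetes, and BMI". It covers the cross-sectional and the longitudinal part alike. The section does not say when hypertension is measured, or whether a total or a direct effect is meant.

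The rest of the article gives hypertension a different role:

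- Background: "because some workers perform occupational lifting for several hours per day, many days per week, higher BP or hypertension is likely to occur".
- Objective, for the cross-sectional analysis: "the primary null-hypothesis is that there is no association between heavy occupational lifting and hypertension". Hypertension is the outcome there.
- Implications of the Proposed Analysis: "a positive association could be considered as a reflection of a physiological mechanism".
- Background again: "Hypertension is a major risk factor for cardiovascular diseases".

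Background also records the opposite possibility, that "heavy lifting might also impose beneficial effects on BP".

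**The concern.** A confounder is a cause of the outcome that is associated with the exposure and is not its consequence. In the main study hypertension is the hypothesised consequence of lifting; in the substudy the same variable is listed as a confounder of lifting. Both roles can hold only if the substudy means hypertension that came before the lifting, and it does not say so.

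Conditioning on a consequence of exposure that lies on the way to the outcome changes the quantity estimated. The coefficient for lifting becomes the association not carried by the hypertension variable. A reader of the results would take it for the association between lifting and cardiac damage, because that is the declared aim and the adjustment is labelled as control of confounding. The Discussion links the study to prevention, for which the total association is the more relevant quantity.

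**Working it through.** **Step 1. The two links, from the article's own text.**

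| Link | Where the article asserts it |
|---|---|
| Lifting to hypertension | Background (rationale), Objective (null hypothesis), Implications (a positive result would be read as physiological) |
| Hypertension to heart | Background (major risk factor for cardiovascular disease) |
| Hypertension as confounder of lifting | Substudy on Cardiac Damage only |

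The first two rows together make hypertension a mediator under the working hypothesis. The third row conflicts with them unless timing is specified.

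**Step 2. The substudy's power figure.** Inputs from the substudy section: 200 per group, a difference of 1 in global longitudinal strain, alpha 1.25%, power 80%. No SD and no sidedness are given, so the 80% cannot be reproduced independently. It can be solved backwards, assuming a two-sided test:

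- z(1 − 0.0125/2) + z(0.80) = 2.498 + 0.842 = 3.339
- standard error = 1/3.339 = 0.2995
- SD = 0.2995/√(2/200) = 2.99

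A one-sided test would imply an SD of 3.24. With an SD of 3.0, two-sided power is 79.8%, so the stated figure is coherent with an SD of about 3.

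**Step 3. Power for what remains after adjustment.** Assume a total difference of 1 and an SD of 2.99 unchanged by adjustment (standard error 0.299). The mediated share m is an assumption; the documents give none. The remaining effect is 1 − m, and power = Φ((1 − m)/0.299 − 2.498).

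| m | Remaining effect | Power |
|---|---|---|
| 0% | 1.00 | 80% |
| 10% | 0.90 | 70% |
| 25% | 0.75 | 50% |
| 50% | 0.50 | 20% |

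**Step 4. Which shares are plausible?** As an illustration, apply the 20% hypertension prevalence from Statistical Power to the unexposed. Assume an odds ratio of lifting for hypertension, and assume that hypertension shifts strain by 1 to 2 units. The mediated part is (p1 − 0.20) × shift, where the odds p1/(1 − p1) equal 0.25 × the odds ratio. Because the total is 1, the mediated part is also the share.

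| Odds ratio | p1 | Mediated part | Power for the rest |
|---|---|---|---|
| 1.2 | 0.231 | 0.03 to 0.06 | 77% to 74% |
| 1.5 | 0.273 | 0.07 to 0.15 | 73% to 64% |
| 2.0 | 0.333 | 0.13 to 0.27 | 66% to 48% |

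On these inputs a 25% share is reached only at the extreme corner, and 50% not at all.

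**Step 5. Direction.** Take a direct effect of 0.5 and a hypertension shift of 2.

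- Odds ratio 2: total = 0.5 + 2 × (0.333 − 0.20) = 0.77. Adjustment returns about 0.5, so the estimate moves toward zero.
- Odds ratio 0.5: p1 = 0.125/1.125 = 0.111, and total = 0.5 + 2 × (0.111 − 0.20) = 0.32. Adjustment again returns about 0.5, so the estimate moves away from zero.

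Simulation of the same linear model agrees: 0.77 to 0.51 in the first case, 0.33 to 0.51 in the second.

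**The case against.** The strongest reply is that the substudy speaks only of associations and declares no total-effect target. Adjusting for hypertension is legitimate if the question is whether lifting harms the heart by other routes, and Background describes large acute pressure rises during lifting that need not pass through resting hypertension. In the longitudinal part, hypertension present before the exposure can be a genuine confounder, and the primary prospective analysis itself adjusts for baseline BP. The section is one paragraph in a condensed article, and further models may be described in a fuller plan.

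Much of this stands as a limit on the claim. A reader might infer that adjustment necessarily biases the result toward zero, removes the whole pathway, or turns real damage into a report of none. The documents do not support that:

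- The direction depends on whether lifting raises or lowers BP.
- Only what the hypertension variable captures is removed.
- An effect vanishes only under near-complete mediation.

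Nor does the article say whether the difference of 1 used for power is adjusted or unadjusted, so the power losses are illustrations and not a demonstrated error in the 80%.

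The reply does not remove the contradiction. The label is confounder, with no timing and no direct-effect target. The point rests on what the article states, not on what it leaves out.

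**Conclusion.** The point holds in this form: the substudy's only described model conditions on a variable that the article's own hypothesis places on the path from lifting to cardiac damage, and calls this control of confounding. If lifting raises BP and hypertension harms the heart, the adjusted estimate understates the total association; if lifting lowers BP, it shifts the other way. In both cases it is not the total association.

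The size cannot be computed from the documents. The range in the working (80% power falling to 70%, 50% or 20% for shares of 10%, 25% or 50%) rests on an assumed two-sided test, a total difference of 1, an SD of about 3.0 unaffected by adjustment, and assumed shares, of which the smaller ones are plausible. The structural conflict depends on none of these values. It concerns the interpretation of the substudy and leaves the two primary hypotheses untouched.

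**What to change.** - **Main substudy model:** the age- and sex-matched comparison adjusted for smoking, education, BMI and diabetes, without hypertension or BP measured at the same time as or after the exposure. Name the covariates individually: a reference to the primary model would be ambiguous, because the primary prospective model includes baseline BP and neither primary model includes diabetes. The article hypothesises no effect of lifting on BMI or diabetes, so this argument gives no reason to drop them.
- **Second model:** the same with hypertension added, labelled as the association not explained by hypertension.
- **Longitudinal part:** treat hypertension as a confounder only where it is known to precede the exposure. The exposure question covers the past year, so a reading at the same examination does not establish the order.
- **Power statement:** say which model the difference of 1 refers to.

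The cost is one extra model on data already planned, plus a stated change in the main adjustment set. The small downside is that the main estimate also carries hypertension that lifting did not cause, which is why both models should be shown.

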## Results

### Flow of Participants

In the third examination in 1991-1994, 10,135 out of 16,560 (61.20%) participants attended; in the fourth examination in 2001-2003, 6237 out of 12,599 (49.50%) participants attended; and in the fifth examination in 2011-2015, 4550 out of 9765 (46.59%) participants attended. On the basis of the inclusion criteria of responding to the level of OPA, 5031 observations were excluded from examination 3; 2600 from examination 4; and 1621 from examination 5. Hence, the final populations for the cross-sectional and prospective analysis are assumed to include less than 7166 participants in the cross-sectional analysis and less than 1850 participants in the prospective analysis (Figure 3), due to the additional inclusion criteria of measured BP and use of antihypertensive drugs. The information on BP and use of antihypertensive drugs will be provided after submission of this protocol paper.

### Descriptive Information of the Included Population

The population which will be included in the analysis will be set by the criteria for inclusion, described previously. Therefore, it is assumed that fewer participants will be included in the analysis than the amount of participants answering on the level of OPA, described in Tables 7 and 8.

### Differences in the Study Population

Smaller numerical differences were observed between the participants answering on the level of OPA and the attending participants.

Cross-sectionally, the participants responding to the level of OPA were 9.8 years younger (mean age 49.0 years among the participants answering on the level of OPA and 58.8 years among the attending), had a higher level of education than the attending participants (13.87% [1619/11,670] participants responding to the level of OPA were noneducated and 20.69% [4328/20,922] among the attending), and a higher proportion of the participants responding to the level of OPA stated to be exposed to heavy occupational lifting (14.04% [1638/11,670] among the participants responding to the level of OPA and 8.48% [1774/20,922] among the attending participants).

**Figure 3 figure3:**
[figure not shown]
Flow of the observations and participants in the third, fourth, and fifth examinations of the Copenhagen City Heart Study. OPA: occupational physical activity; obs: observation.

**Table 7 table7:** Baseline characteristics of the participants responding to the level of occupational physical activity for the cross-sectional analysis; 11,670 observations on 7166 participants.

Cross-sectional analysis		Mean (SD)	n (%)	Range
Age (years)		49.0 (13.8)		20.3-99.7
Sex (% female)			5330 (54.3)	
Body mass index (kg/m^2^)		25.2 (4.3)		12.8-56.6
Smoking (% current smokers)			4292 (36.9)	
**Education**				
	Uneducated		1619 (14.1)	
	Low educated, <3 years		1806 (15.7)	
	Vocational education, 1-3 years		3123 (27.2)	
	Higher education, >3 years		2103 (18.3)	
	Academic education		2837 (24.7)	
**Occupational physical activity**				
	Predominantly sedentary		4407 (37.8)	
	Sitting or standing, some walking		4079 (35.0)	
	Walking, some handling of material		2729 (23.4)	
	Heavy manual work		455 (3.9)	
Occupational heavy lifting (% yes)			1830 (15.7)	
Vital exhaustion (sum, 0-17)		3.0 (3.5)		0-17
Cardiorespiratory fitness (% similar level as peers)			6390 (54.8)	
Observation per participant		2.0 (0.8)		1-3

Prospectively, the participants answering on the level of OPA were 11.0 years younger (mean age 48.0 years among participants responding to the level of OPA and 59.0 years among the attending). The smokers were 2.31 percentage points higher (38.96% [2311/5932] of the participants responding to the level of OPA were current smokers and 36.65% [6930/18,908] among the attending); they had a higher level of education than the attending participants (12.39% [735/5932] of the participants responding to the level of OPA were noneducated and 19.76% [3737/18,908] among the attending). A higher proportion of the participants responding to the level of OPA stated to be exposed to heavy occupational lifting (17.52% [1039/5932] among the participants responding to the level of OPA and 8.34% [1576/18,908] among the attending participants), and a higher proportion of the participants responding to the level of OPA stated to have a level of cardiorespiratory fitness similar to their peers (57.67% [3421/5932] among the participants responding to the level of OPA and 45.57% [8617/18,908] among the attending).

These nonsignificant differences between the attending participants and participants responding to the level of OPA in the cross-sectional and prospective populations may affect the prevalence of hypertension. The younger age of the participants responding to the level of OPA as well as their higher proportion of being educated might lower the prevalence of hypertension among these participants compared with those attending [28]. Conversely, may those participants responding to the level of OPA have a higher prevalence of hypertension due to their higher exposure to heavy occupational lifting than among the attending participants. In the prospective population, the small difference in proportion of participants stating to have a level of cardiorespiratory fitness similar to their peers, is not believed to affect the prevalence of hypertension, as the proportion of participants stating to have a higher level of cardiorespiratory fitness than their peers is similar among those participants responding to the level of OPA and those attending.

**Table 8 table8:** Baseline characteristics of the participants responding to the level of occupational physical activity for the prospective analysis; 5932 observations on 4089 participants.

Prospective analysis		Mean (SD)	n (%)	Range
Age (years)		48.0 (11.8)		20.3-84.3
Sex (% female)			3301 (55.7)	
BMI (kg/m^2^)		25.0 (4.0)		16.0-52.5
Smoking (% current smokers)			2311 (39.1)	
**Education**				
	Uneducated		735 (12.6)	
	Low educated, <3 years		2142 (36.7)	
	Vocational education, 1-3 years		1983 (34.0)	
	Higher education, >3 years		380 (6.5)	
	Academic education		590 (10.1)	
**Occupational physical activity**				
	Predominantly sedentary		2113 (35.6)	
	Sitting or standing, some walking		2086 (35.2)	
	Walking, some handling of material		1497(25.2)	
	Heavy manual work		234 (3.9)	
Occupational heavy lifting (% yes)			1039 (17.5)	
Vital exhaustion (sum, 0-17)		2.9 (3.3)		0-17
Cardiorespiratory fitness (% similar level as peers)			3421 (57.7)	
Observation per participant		1.5 (0.5)		1-2

## Discussion

### Study Protocol

This study aims to contribute to the knowledge of risk for hypertension from heavy occupational lifting, and possibly thereby contribute to the prevention of cardiovascular disease by giving recommendations for participants exposed to heavy occupational lifting.

### Implications of the Proposed Analysis

Since one-third of the workforce in Europe reports to carry or move heavy loads regularly during working hours (6th survey in Eurofound) and hypertension is a major risk factor for cardiovascular disease and mortality [1;2], a positive association between occupational lifting and risk for hypertension could reveal a potential for improved prevention for hypertension by reducing exposure to occupational lifting in the population. This could, for example, be achieved by using technical lifting devices and automatization of manual work tasks currently requiring heavy lifting. This is particularly the case because a positive association could be considered as a reflection of a physiological mechanism and therefore must be assumed to apply for the majority of humans exposed to occupational lifting. Conversely, a negative association would not be assumed as a reflection of a physiological mechanism before the negative association had been verified in populations not subject to restrictive regulations of occupational lifting, as employees in Denmark are. Moreover, a null finding would also propose a need for additional investigations of this association in populations with wider ranges of exposure to occupational lifting. Since these proposed analyses will be applied to a randomly selected adult population and is planned to be verified in another randomly selected adult Danish population, these results may be generalized to the Danish adult population engaged in work including occupational lifting.

